## Methods

### Study objective, design, and setting

The primary objective of the ENSURE-GA study is to evaluate the effect of an intervention based on a standardized GA on patient satisfaction with their treatment. This study will be a phase III comparative clinical trial with a cluster-randomized design and will be conducted in 81 medical facilities that have been selected based on the following four factors: (i) number of beds ( ≧ 200 beds or < 200 beds); (ii) whether or not designated as a cancer hospital by the Japanese Ministry of Health, Labor, and Welfare; (iii) region (divided into 6 regions, and these regions were evenly allocated with participating facilities from each region); and (iv) whether GA is usually included in medical treatment. Each facility will be randomly allocated in order of enrollment to the intervention or non-intervention group in a 1:1 ratio.

The primary endpoint will be the change in patient satisfaction according to the Health Care Communication Questionnaire (HCCQ) questionnaire between the GA and 3 months later. The secondary endpoints will be (i) the change in the quality of life; (ii) the treatment completion rate; (iii) the proportion of participants showing improvement by at least one grade in their Eastern Cooperative Oncology Group performance status (ECOG-PS); (iv) the relationship between the pre-chemotherapy risk assessment results and adverse events, evaluated separately for cytotoxic anticancer agents, molecular-targeted agents, and immune checkpoint inhibitors; and (v) the proportion of screened patients who had vulnerability factors in at least one of the GA tools and are enrolled in the study.

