We have built a GA tool as an iPad application and have developed a system that displays GA results and recommendations for related interventions. Using this system, GA is performed for each participant. In the intervention facilities, participants’ GA results and the intervention method recommended on the basis of these results will be displayed immediately on the iPad in the form of a report. Using this report, the responsible physician will explain the GA results and the intervention method to the participant (Table 1). In the non-intervention facilities, the physician will perform a GA, but the results and the intervention method recommended based on these results will not be displayed on the iPad. The physician will decide on treatment solely on the basis of the ECOG-PS and multiple-organ function, as is currently the standard for lung cancer treatment in Japan. Patients who are analyzed for the primary endpoint are those with one or more vulnerability factors identified using the GA tools. All participants will complete a patient satisfaction survey before treatment initiation and 3 months later (Fig. 1). The ENSURE-GA study is an intergroup trial, and the North East Japan Study Group and CS-Lung are working together to conduct the trial.

**Table 1 Tab1:** Geriatric assessment tools and examples of possible interventions based on the assessment results

Evaluated items	Recommended GA tools	Example of intervention (support) method based on the GA results
Physical function: Falls	• Lawton IADL • “How many times have you fallen during the last 6 months?”	• Referral to an occupational therapist and/or physiotherapist • Prevention of falls • Evaluation of safety of home and garden
Complications, polypharmacy	• CCI • Number of drugs in regular use	• Encouraging involvement of family members in management of complications • Collaboration between the primary-care physician and a geriatrician • Consulting a pharmacist regarding reducing the number of medications
Cognitive function	• Mini-Cog	• Evaluation of decision-making capability • Selection of someone with power of attorney, if necessary • Collaboration between a geriatrician and a cognitive function specialist • Prevention of delusions, by adjusting medication
Depressive state	• GDS	• Referral to a psychiatrist • Promoting participation in social activities • Prescription of an antidepressant
Nutrition	• BMI below 21 kg/m^2^	• Referral to a dietician • Provision of support for preparing meals

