### Inclusion and exclusion criteria

Participants will be required to meet all of the following inclusion criteria:

histologically and/or cytologically confirmed to have non-small-cell lung cancer,radical resection-radiotherapy and radical chemotherapy are not feasible,age at least 75 years,ECOG-PS of 3 or less, and.provide informed consent for participation.

Patients with any of the following factors will be excluded from the study:

dementia and aggressive cancer treatment,psychiatric disorders that could interfere with participation, and.study participation is judged by the responsible physician to be inappropriate for any other reason.

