## Sample size

For calculating the required number of subjects, first, the number needed for randomization of individual subjects will be calculated, followed by the number needed for cluster randomization. With reference to a report by Mohile et al. [6], it is predicted that the mean scores in the HCCQ Patient Satisfaction Survey before chemotherapy will be 23.3 and 22.2 in the intervention and non-intervention groups, respectively. Considering the common standard deviation for this variable to be 4.5, the two-sided α error to be 5 %, and the detection power to be 80 %, the required number of subjects is calculated to be 526.

Taking the required number of subjects for separate randomization to be *n*, the required number for cluster randomization to be *n’*, the cluster size to be *m*, and the intra-cluster correlation coefficient to be *ρ*, the formula is as follows:
$$n' = ([m - 1] \rho + 1) n$$

Using the above formula, taking *n* to be 526, *m* to be 15, and *ρ* to be 0.05 yields a value of 895 for *n’*, and a required number of clusters of 60; therefore, the number of study sites has been set at a minimum of 60. We assumed that 10 % of prospective participants would have at least one exclusion criterion, and thus the minimum number of participants required is 985.

In addition, in a previous study by our research group, it was found that, among lung cancer patients aged over 75 years, 97 % showed at least one vulnerability factor (unpublished data). Taking this into consideration, the sample size has been set at 1020. Eighty-one medical facilities (study sites) distributed throughout Japan have been selected for the study. We aim to enroll 15 participants per site.

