### Statistical analysis

A mixed-effects model will be used to perform intergroup comparisons taking intra-cluster correlation into consideration, and the 95 % confidence interval will be calculated. Statistical analyses are performed using the Statistical Analysis System, version 9.4 (SAS Institute Inc., NC, USA).

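### Secondary endpoint (iii) counts patients who enter at ECOG-PS 0 as certain non-improvers, so its rate mixes entry PS with improvement

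*Protocol article*

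**What the plan says.** In the Protocol article, under Study objective, design, and setting, the third secondary endpoint is "the proportion of participants showing improvement by at least one grade in their Eastern Cooperative Oncology Group performance status". The denominator is participants, with no qualifier on entry status.

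Under Inclusion and exclusion criteria, the performance-status rule is "ECOG-PS of 3 or less". That is an upper limit only, so grades 0 to 3 are eligible.

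One restriction on the analysed patients is stated: "Patients who are analyzed for the primary endpoint are those with one or more vulnerability factors identified using the GA tools". It concerns the primary endpoint and rests on the GA tools, not on PS.

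Randomization is by site: "Each facility will be randomly allocated in order of enrollment to the intervention or non-intervention group in a 1:1 ratio". The four factors listed just before that sentence (bed number, cancer-hospital designation, region, and "whether GA is usually included in medical treatment") describe facilities. None is a patient's PS.

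Under Statistical analysis, the model is given in one sentence: "A mixed-effects model will be used to perform intergroup comparisons taking intra-cluster correlation into consideration". Entry PS is not mentioned.

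**The concern.** Grade 0 is the best ECOG grade. A patient who starts there is a non-improver whatever happens during the trial, yet still counts in the denominator. The fault lies in who is counted, not in the one-grade threshold.

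Two things follow. First, the absolute difference between arms is smaller than the difference among patients in whom improvement is possible. Second, the rate depends on how many PS 0 patients each arm enrols. If the arms differ in that share, a difference can appear without any effect, or a real one can be partly hidden. A site random effect allows for correlation within sites but does not correct a difference in entry PS between arms.

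At stake is the reading of one secondary endpoint.

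**Working it through.** **The plan's own figure.** The document gives no rate, effect or power for endpoint (iii). Its only calculation is for the primary endpoint, with means of "23.3 and 22.2 in the intervention and non-intervention groups" (difference 1.1), SD 4.5, two-sided 5% and 80% power:

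- Per arm: 2 x (1.96 + 0.84)^2 x 4.5^2 / 1.1^2, which rounds up to 263, so 526 in total, as stated.
- Design effect: (15 - 1) x 0.05 + 1 = 1.7, and 526 x 1.7 = 894.2, stated as 895.

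Both reproduce. Only the planned 1020 patients (510 per arm), the cluster size of 15 and the ICC of 0.05 are carried over below. Applying that ICC to PS improvement is an assumption.

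**Form of the endpoint.** Let q be the share of an arm at entry PS 0 and r the improvement rate among entry PS 1 to 3. The arm rate is (1 - q) x r.

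**Equal PS 0 shares.** The risk difference is (1 - q)(r1 - r2). The risk ratio is r1/r2, because (1 - q) cancels. Assume r = 30% vs 20%. Power is taken as Φ(difference/SE - 1.96), with SE = √{[a(1 - a) + b(1 - b)]/n_eff} for arm rates a and b.

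- All enrolled counted: n_eff = 510/1.7 = 300 per arm.
- Entry PS 1 to 3 only: n_eff = 510(1 - q)/[1 + (15(1 - q) - 1) x 0.05].

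At q = 10%:

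- All enrolled: 27% vs 18%, SE = √[(0.1971 + 0.1476)/300] = 0.0339, 0.09/0.0339 = 2.66, power about 76%.
- PS 1 to 3: n = 459, design effect 1.625, n_eff = 282, SE = √(0.37/282) = 0.0362, 0.10/0.0362 = 2.76, power about 79%.

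| PS 0 share, both arms | Difference, all enrolled | Power, all enrolled | Power, PS 1 to 3 |
|---|---|---|---|
| 10% | 9 points | 76% | 79% |
| 20% | 8 points | 69% | 76% |
| 30% | 7 points | 62% | 72% |
| 40% | 6 points | 54% | 68% |

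The gap of 14 points in the last row owes most of its size to holding the ICC at 0.05 while clusters shrink from 15 to 9. Without clustering, the same row gives:

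- All enrolled: 18% vs 12% with 510 per arm, 0.06/0.0223 = 2.69, power 77%.
- PS 1 to 3: 30% vs 20% with 306 per arm, 0.10/0.0348 = 2.88, power 82%.

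That is a gap of about 5 points.

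**Unequal PS 0 shares.**

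- No effect, r = 20% in both arms, shares of 20% vs 30%: 0.80 x 20% = 16% against 0.70 x 20% = 14%. Two points appear from entry mix alone.
- True 30% (intervention) vs 20% (control), with shares of 30% and 20% respectively: 0.70 x 30% = 21% against 0.80 x 20% = 16%. Five points are seen, where a common share of 20% or 30% would show 8 or 7.

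**The case against.** The strongest reply is that this is one clause in a condensed article. Evaluable sets and covariates for a secondary endpoint are commonly left to the full protocol or SAP, which may restrict the denominator or adjust for entry PS. As to the covariate, that is right: its absence is no fault by itself. But the population of the endpoint is stated, as participants, and with the stated eligibility range it includes patients whose result is fixed at entry. That wording can be improved whatever an unseen document says.

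It can also be said that the share of an enrolled population that improves is a legitimate quantity, truly smaller when some cannot benefit. That stands. With equal shares, the shrinkage is a matter of which effect is being estimated, not bias, and the risk ratio does not move.

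As to imbalance, chance alone would do little. With 300 effective patients per arm and a PS 0 share near 20%, the standard error of the gap in shares is √(2 x 0.2 x 0.8/300) = 3.3 points, which moves the rate by 0.20 x 3.3 = 0.7 points. Even the example of 20% vs 30% is a gap of 10/3.5 = 2.8 standard errors, and its 2 spurious points sit below the roughly 3.0-point standard error of the endpoint difference itself (√(2 x 0.16 x 0.84/300)). Chance imbalance is also already reflected in the confidence interval. This stands too. A larger gap, such as 10% vs 30%, would be extreme and would need strong selective enrolment.

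A reader might infer such selection because sites are randomized and only intervention sites see the GA report. The article does not say that staff recruit knowing their arm, and it gives no reason why arms would differ at PS 0. The design does not rule imbalance out; it does not show it.

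Finally, restricting the denominator does not by itself equalize the mix of PS 1, 2 and 3. That is correct, and is why the fix also includes entry PS as a covariate.

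**Conclusion.** The point holds in a limited form. As worded, endpoint (iii) equals (1 - PS 0 share) times the improvement rate among those who can improve. With equal shares, the absolute difference shrinks by (1 - PS 0 share) and the risk ratio is unchanged. The power cost is about 3 points at a 10% share under the assumed 30% vs 20% and ICC of 0.05. With unequal shares, entry mix enters the comparison: 2 points under no effect for shares of 20% vs 30%.

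The PS 0 share, the improvement rates and the ICC for this endpoint are all assumptions, since the document gives none of them. Two stronger readings are not supported. A reader might conclude that the endpoint is already biased between arms, but no imbalance is documented. A reader might also conclude that power is heavily damaged, but the larger gaps need a high PS 0 share and come mostly from the fixed ICC. The primary endpoint, its sample size and the main conclusion are untouched. The change is worth making because it is cheap and gives a clearer endpoint.

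**What to change.** - Define endpoint (iii) as the proportion improving by at least one ECOG-PS grade among participants with entry ECOG-PS of 1 or more.
- Compare arms in the planned mixed-effects model, in logistic form with a site random effect, with entry PS (1, 2, 3) as a categorical covariate.
- Report the entry PS distribution by arm, including the PS 0 share, beside the result.

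The cost is one sentence in the endpoint list and a line in the analysis text. Entry PS is already needed for eligibility, so no extra patients, visits or data are required. The small downside is that PS 0 patients leave this one secondary analysis, and the estimate then applies to patients who can improve rather than to everyone enrolled.

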**Fig. 1 Fig1:**
[figure not shown]
Study flowchart summarizing the study procedures. Abbreviations: BSC, best supportive care; ECOG-PS, Eastern Cooperative Oncology Group performance status; GA, geriatric assessment; QOL, quality of life

Ethics approval will be obtained from the ethics committee of each participating institution. All patients will sign an informed consent form before inclusion. The study has been registered in the University Hospital Medical Information Network database (no. UMIN000037590).

### Inclusion and exclusion criteria

Participants will be required to meet all of the following inclusion criteria:

histologically and/or cytologically confirmed to have non-small-cell lung cancer,radical resection-radiotherapy and radical chemotherapy are not feasible,age at least 75 years,ECOG-PS of 3 or less, and.provide informed consent for participation.

Patients with any of the following factors will be excluded from the study:

dementia and aggressive cancer treatment,psychiatric disorders that could interfere with participation, and.study participation is judged by the responsible physician to be inappropriate for any other reason.

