**Methods:**

The study will be a phase III comparative clinical trial with a cluster-randomized design, and it will be conducted at 81 sites distributed throughout Japan. Approximately 1000 lung cancer patients aged ≥ 75 years will be enrolled in the study. All participants will undergo a standardized GA before starting treatment (using an iPad). At the intervention sites, the GA results and intervention method recommended on the basis of the GA results will be returned as an instant report to guide the physician’s choice of intervention. At the control sites, the physician will decide on interventions based on standard practice. All participants will complete a patient satisfaction survey before treatment initiation (after the GA) and 3 months later.

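### Enrolment is open to selection after allocation: a physician who can see the site's arm, and who must explain the report at intervention sites, may exclude patients on open-ended grounds

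*Protocol article*

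**What the plan says.** All references are to the protocol article.

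- **Allocation** (*Study objective, design, and setting*): "Each facility will be randomly allocated in order of enrollment to the intervention or non-intervention group in a 1:1 ratio". The four factors listed there (bed number, cancer-hospital designation, region, usual use of GA) describe facilities, not patients.
- **Visibility of the arm** (same section): intervention sites get the report at once. At the other sites, "the results and the intervention method recommended based on these results will not be displayed on the iPad".
- **Who delivers the intervention** (same section): at intervention sites "the responsible physician will explain the GA results and the intervention method to the participant".
- **Entry of patients** (paragraph below Fig. 1): "All patients will sign an informed consent form before inclusion".
- **Discretion** (*Inclusion and exclusion criteria*): the last exclusion applies when "study participation is judged by the responsible physician to be inappropriate for any other reason".
- **Primary analysis set** (*Study objective, design, and setting*): "Patients who are analyzed for the primary endpoint are those with one or more vulnerability factors identified using the GA tools". The abstract states that every participant has the same standardised GA before treatment, and *Sample size* expects 97% to have at least one such factor.
- **Analysis** (*Statistical analysis*): a mixed-effects model that allows for intra-cluster correlation.

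**The concern.** A catch-all exclusion is common and, on its own, harmless. Here it meets two other features. The person applying it can see the arm, and in one arm only a further task follows from enrolling the patient: explaining the report and its recommendations. A physician at an intervention site might pass over patients who are hard to counsel, or favour those likely to welcome the report. A physician at a control site has neither motive.

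If this happens, the arms differ in who was enrolled as well as in what was done, and the primary comparison mixes the two. A mixed model for intra-cluster correlation gives an appropriate standard error for clustered data but leaves such a difference in the point estimate. More sites or patients would shrink the standard error and not the bias.

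**Working it through.** **1. The plan's own figures.** Inputs from *Sample size*: means 23.3 and 22.2 (difference 1.1), SD 4.5, two-sided 5%, power 80%, cluster size 15, intra-cluster correlation 0.05.

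- Per arm: 2 × (1.960 + 0.842)² × 4.5² / 1.1² = 262.7, so 263, or 526 in total.
- Design effect: 1 + 14 × 0.05 = 1.70. Then 526 × 1.70 = 894.2, set at 895; 894.2 / 15 = 59.6, so 60 clusters.
- 895 × 1.10 = 984.5, so 985; 985 / 0.97 = 1015.5, set at 1020.

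The stated sizes reproduce. The point is about bias, not size.

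**2. Shift from unequal enrolment.** Let q be the extra share of eligible patients left out in one arm, and D the difference in mean HCCQ change between those left out and those kept. The mean in that arm moves by b = q × D. The document gives neither q nor D. Assumed ranges: q = 5-10% (the plan itself allows for 10% meeting an exclusion criterion) and D = 0.5-1 SD, that is 2.25-4.5 points, taking the planned SD of 4.5 to apply to the change score.

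**3. Effect on the test.** SE = 4.5 × √(4 × 1.70 / 895) = 0.392. With no true effect, the rejection probability is 1 − Φ(1.96 − b/SE) + Φ(−1.96 − b/SE).

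| q | D | b = q × D | b / 1.1 | Rejection probability |
|---|---|---|---|---|
| 0 | – | 0 | 0% | 5.0% |
| 5% | 2.25 | 0.11 | 10% | 5.9% |
| 5% | 4.5 | 0.225 | 20% | 8.8% |
| 10% | 2.25 | 0.225 | 20% | 8.8% |
| 10% | 4.5 | 0.45 | 41% | 20.9% |

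These rates are the same whichever arm the shift favours. If the true effect is 1.1 and the shift runs against it, power falls instead: at b = 0.45 the expected difference is 1.1 − 0.45 = 0.65, 0.65 / 0.392 = 1.66, and power is about 38%.

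**4. The same check for the analysis set.** The vulnerability rule removes about 3%. Even if those patients were dropped in one arm only and differed by a full SD, the shift would be 0.03 × 4.5 = 0.135 points, with a rejection probability of 6.4%.

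**The case against.** *The article condenses a fuller protocol.* Consecutive screening, screening logs and covariates commonly sit in the full protocol or the analysis plan, so their absence here is no finding. This stands. The point rests on what is stated: a visible arm and an open-ended exclusion held by the physician. If safeguards exist, citing them settles the matter. The secondary endpoint based on screened patients suggests that some screening count is kept, though not that reasons are recorded.

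*The order of events is inferred.* No sentence says that patients are identified after their site is allocated. This also stands, although it is the natural reading of facilities allocated in order of enrolment and of a display that depends on the arm.

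*The outcome is a change from baseline.* Stable differences in satisfaction level cancel, so D must be a difference in change, for which the document gives no figure. This is why the size above is only an illustration. The direction is open too: if frail patients gain most and are left out at intervention sites, the bias runs towards no effect.

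*A stronger reading is tempting.* A reader might infer that the physician also decides who enters the primary analysis, or that cluster randomisation gives the patient comparison no protection. The document supports neither. Entry to the primary set follows one rule, on a standardised pre-treatment GA used in both arms, and about 97% are expected to meet it. What remains there is arm-aware administration of the GA, which step 4 shows has little room to matter. Randomisation still balances sites, and the patients they serve, in expectation; only arm-dependent enrolment is at issue.

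**Conclusion.** The concern holds for enrolment. Site staff can see the arm, and the responsible physician, who must explain the report at intervention sites, may exclude patients on open-ended grounds. Neither site-level randomisation nor the planned allowance for clustering removes an imbalance that arises in this way.

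The size is not known. Under the assumed 5-10% extra exclusions and 0.5-1 SD difference in change, the shift is 0.11-0.45 points, or 10-41% of the planned effect, and the false-positive rate at N = 895 is about 6-21%. The conclusion rests on the inferred order of allocation and enrolment, on the planned SD holding for the change score, and on there being no safeguards in the full protocol. Differential enrolment is a risk that the design permits; nothing shows that it has occurred. The remedies are cheap and protect the primary comparison, so they should be adopted.

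**What to change.** (a) At every site, approach consecutive eligible patients. Record each discretionary exclusion and its reason before the GA is opened on the iPad, and report these by arm. Cost: a short log per site.

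(b) Add pre-specified patient-level baseline covariates to the primary mixed model: age, ECOG-PS, Geriatric 8 and Charlson index. The trial already collects all four, so the cost is analysis wording. This reduces imbalance on measured factors only, so it supplements (a) and does not replace it.

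Keep patients with at least one vulnerability factor as the primary set. An analysis of all enrolled patients is worth adding as a sensitivity analysis at most. If the full protocol already has recruitment safeguards, it is enough to cite them.
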